**Secondary outcome parameter:**

*Personal recovery*

Quality of life will be assessed with the *Manchester Short Assessment of Quality of Life (MANSA; 16 items; Priebe et al., 1999)*. The MANSA is a shortened version of the Lancashire Quality of Life Profile (LQLP; Oliver, 1991), and was specially developed for measuring quality of life in patients with psychological problems. The instrument consists of 16 items, including the satisfaction with work / unemployment, the quality of friendships and mental health on a seven-point scale (from "can not be worse" to "can not be better"). In addition, there are four questions answered with 'yes' or 'no', such as the presence of a good friend. The MANSA is completed by the client.

I.ROC. The Individual Recovery Outcomes Counter (I.ROC) is a twelve-item facilitated questionnaire and is found to be a valid and reliable measure of recovery in mental health (Monger et al., 2013). That is, the I.ROC showed high internal consistency. Exploratory factor analysis indicated a two-factor structure comprising intrapersonal recovery (factor 1) and interpersonal recovery (factor 2), explaining between them over 50% of the variance in I.ROC scores. The I.ROC significantly correlated with widely used existing instruments assessing both personal recovery and clinical outcomes (resp. Recovery Scale (RAS) and the Behaviour and Symptom Identification Scale (BASIS-32)).

*Societal recovery*

Basic demographics, family history, socio-economic status, lifetime psychiatric illness diagnosis and psychiatric history (including number of compulsory admissions) will be enquired. Moreover, several questions regarding education, work, social network and frequency and importance of social contact are included to obtain objective information regarding social and societal functioning. Also, the following questionnaires will be collected:

General, social and societal functioning will be assessed with the *WHODAS 2.0 - 36*, interview version (Üstün, Kostanjsek, Chatterji & Rehm, 2010). The WHODAS 2.0 - 36 consists of 36 items produces standard disability measures across six domains: Cognition, mobility, self-care, getting along, life

activities and participation (World Health, 2014). The WHODAS 2.0 - 36 items has shown good psychometric properties in clinic and rehabilitation samples (Garin et al., 2010). Moreover, the questionnaire is responsive to pick up changes in the functioning profiles over time (Üstuün et al., 2010).

Additionally, to measure general functioning, the *Global Assessment of Functioning (GAF)* will be scored by the interviewer in line with previous work on the RG (Malm et al., 2014). The GAF outcome measures are the DSM-IV split-GAF disability and split-GAF symptoms rating scales (scores range from 100 (extremely high functioning) to 1 (severely impaired)). Research has suggested the GAF as a valuable outcome indicator (Gaite et al., 2005; Pedersen & Karterud, 2012).

The individual's level of social and occupational functioning will be assessed with the *Social and Occupational Functioning Assessment Scale (SOFAS)* (Goldman, Skodol & Lave, 1992), rated by the researcher. The SOFAS scale is similar to the frequently used GAF-score, but it only focuses at social and occupational functioning rather than also considering symptom severity.

#### *Clinical Recovery*

General psychopathological symptoms as an index of severity of syndromal disorders will be assessed with the *Brief Symptom Inventory – 18 items* (BSI-18; Derogatis 2001). The BSI- consisting of 53 items- was reduced to the BSI-18 to decrease the average completion time and to improve its structural validity (Derogatis, 2001). A total score over all items can be calculated representing general distress, which is highly correlated with the total score from the BSI ( $r = .90$ ; Andreu et al., 2008; Durá et al., 2006). Moreover, the total score of the BSI-18 is sensitive to change, and captures smaller changes in symptomatology. Therefore, the BSI is considered as a suitable outcome to measure therapy effect (De Beurs and Zitman, 2006). Next to the total score, a dimension score on somatic complaints, depression and anxiety can be obtained with the BSI-18.

#### *Mediating variable*

Attachment Style will be assessed with the *Revised Adult Attachment Scale* (RAAS; Collins, 1996) in order to identify underlying models of attachment as a potential mediating variable. The RAAS has 18 items, divided into 3 sub-scales: trust, support and concern. The psychometric properties of this list range from moderate to good and are described in various articles (Collins, 1996; Tait, Birchwood, & Trower, 2004).

#### *Additional*

The experienced care and burden of the involved RG-members will be assessed with the '*Betrokken Evaluatie Schaal*' (BES; Schene & Van Wijngaarden, 1991). The questionnaire includes four domains (stress, worry, supervision, motivating) and a total score. Questions will be slightly modified in order to use the questionnaire for various mental health disorders- as has been done before (for example van Meijel & Dekker, 2002). The validity and reliability of the BES are satisfactory (Van Wijngaarden, 2003).

For confounding and mediating effects, we will collect information on gender, age, marital state, occupational status, duration of illness, medication use and treatment history.

The use and appreciation of family participation and the RG-method will be assessed by a self-developed treatment satisfaction list that will be filled in by participants, RG-members and professionals. The questionnaire will be divided in two parts. The first part is about generic aspects of family participation and will be assessed in both groups; the second part is about specific RG elements and will only be assessed in the experimental RG group. Central in this questionnaire will be the extent to which the received care in both groups meets the needs of participants and their environment. Themes that will be addressed are: satisfaction with help and support for psychological problems, personal recovery, social relations, daily activities, financial affairs; cooperation and coordination in help and support; support of informal support system; personalized help and support (important matters are addressed); experienced influence and to be taken seriously.

#### *Economic Evaluation*

Use of health services will be assessed with the *Trimbos and Institute of Medical Technology Assessment Cost Questionnaire for Psychiatry* (TIC-P; Hakkaart-van Roijen et al, 2002). With this questionnaire patients register the number of general practice visits, sessions with psychiatrists, hospital admissions, days-in-hospital, compulsory care, contact with teams/services, etc. In addition, the number of 'work loss' days (absenteeism from work) and the number of 'work cut-back' days (reduced efficiency at work while feeling ill) were also measured with help of the TIC-P. Also, information on relapses defined by intake on the DigiBoard of the FACT-team is collected.

Qaly's will be calculated with the *EuroQol EQ-5D-5L* scores, including the EQ-VAS (Herdman et al., 2011; Rabin & Charro, 2001). The EQ-5D-5L is used so that Dutch unit prices can be administered for the valuation of cost prices (as opposed to the often used SF-6D that uses British unit prices) (Oostenbrink, Koopmanschap & Rutten, 2002). Moreover, the ReQol questionnaire has the potential to calculate Qaly's but this process is still ongoing. When there is sufficient scientific support, the ReQoL will be used as an alternative to the EQ-5D-5 to calculate Qaly's.

| Parameters          |          | Test                                                                                                          | Time (min) |
|---------------------|----------|---------------------------------------------------------------------------------------------------------------|------------|
| Primary outcome     | Personal | Netherlands Empowerment List (NEL) (in Dutch: Nederlandse Empowerment Lijst; self-rated)                      | 15         |
| Secondary           | Personal | Recovering Quality of Life, short version 10 items (ReQoL) (self-rated)                                       | 5          |
|                     | Societal | WHO-DAS 2.0 -12 (self-rated)                                                                                  | 5-10       |
|                     |          | Self-reliance matrix (ZRM) (in Dutch: Zelfredzaamheidsmatrix) (observer-rated)                                | 10-15      |
|                     |          | GAF/SOFAS (observer-rated)                                                                                    | 5          |
|                     |          | Demographic information on social network, social contact, societal functioning, part 2 (DEM_2) (self-rated)  | 10         |
| Economic Evaluation | Clinical | Brief Symptom Inventory – 18 items (BSI-18) (self rated)                                                      | 5-10       |
|                     |          | Trimbos and Institute of Medical Technology Assessment Cost Questionnaire for Psychiatry (TIC-P) (self-rated) | 10         |
|                     |          | EuroQol EQ-5D-5L (self-rated)                                                                                 | 3          |

|                                                                  |  |                                                                                                                                                      |
|------------------------------------------------------------------|--|------------------------------------------------------------------------------------------------------------------------------------------------------|
| Mediating                                                 |  | Revised Adult Attachment Scale (RAAS) (self-rated) 5-15
Demographic questionnaire on age, marital status, housing, part 1 (DEM_1) (self-rated) 10 |
| Significant others (filled in by informal support system) |  | Betrokken Evaluatie Schaal (BES) 10                                                                                                           |

Table 1. Questionnaires/interviews that subjects will undergo in the course of the research.

|                                                     | 0
(0months) | 1
(9months) | 2
(18months) |
|-----------------------------------------------------|------------------------|------------------------|-------------------------|
| NEL                                                 | X                      | X                      | X                       |
| ReQoL                                               | X                      | X                      | X                       |
| WHODAS                                              | X                      | X                      | X                       |
| ZRM                                                 | X                      | X                      | X                       |
| GAF/SOFAS                                           | X                      | X                      | X                       |
| DEM_1                                               | X                      |                        |                         |
| DEM_2                                               | X                      | X                      | X                       |
| BSI-18                                              | X                      | X                      | X                       |
| TIC-P                                               | X                      | X                      | X                       |
| EQ-5D-5L                                            | X                      | X                      | X                       |
| RAAS                                                | X                      |                        |                         |
| BES
(filled in by
informal support
system) | X                      | X                      | X                       |

Table 2. Overview of the procedures per assessment moment.

## STATISTICAL ANALYSES:

### Effectiveness RG

Data will be analyzed according to the "intention to treat" principle, including all patients regardless of whether they drop out from treatment or not (StataSE 12.1). We will use Student's t-tests for continuous variables and Pearson chi-squared tests for categorical variables to analyze potential between-condition differences in baseline characteristics. Variables that show different distributions in the conditions, and are correlated with the results, are included in the analysis as a covariate. We will use pre-specified cut-off points of the RG model fidelity checklist to define good adherence.

Primary outcome (empowerment) and secondary outcome parameters are analyzed by means of multilevel mixed regression models with 4 levels: observations within persons, persons within teams and teams within centers. Baseline values of the parameters will be included in the model in order to control for regression to the mean. For categorical outcome variables, counts and in case of non-normal residuals, appropriate forms of mixed regression will be chosen (binomial,

Poisson, gamma, etc). Results are described in accordance with the CONSORT guidelines for randomized controlled trials (Schulz, Altman & Moher, 2010).

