## **Sample size**

Based on the meta-analysis of Nordén and colleagues (2012a), a pre-post effect size of Cohen's  $d = .5$  for the primary outcome is expected. With a sample size of  $N=63$  patients per condition, the study is powered at 80% to detect an effect size of Cohen's  $d = .5$  at a two-tailed significance level of .05. With two conditions we would need to recruit  $N=126$ . Taking into account both repeated measures within a person, assuming a within-correlation of 0.6, and clustering of data (teams; assuming an ICC of .05, health centres; assuming an ICC of 0.1), we will need  $N=133$  patients. Assuming a drop-out of 35%, we will recruit a total of  $N=180$ . There will be 18 participating teams over nine Dutch mental health centres (two teams at each site) and based on rates of incoming patients we expect that a mean of  $N=10$  patients over the course of six months is feasible.

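### Extra covariates for the outcome models are picked by baseline tests and correlation with the results, with no threshold or closed list, so the primary model is not fixed in advance

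*Protocol*

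**What the plan says.** The rule stands in the protocol, Statistical Analyses, "Effectiveness RG". It has two steps.

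- Step one, testing: "We will use Student's t-tests for continuous variables and Pearson chi-squared tests for categorical variables to analyze potential between-condition differences in baseline characteristics".
- Step two, selection: "Variables that show different distributions in the conditions, and are correlated with the results, are included in the analysis as a covariate".

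The next paragraph of that section applies to the primary outcome (empowerment, NEL) and the secondary outcomes. It specifies "multilevel mixed regression models with 4 levels: observations within persons, persons within teams and teams within centers" and fixes one covariate: "Baseline values of the parameters will be included in the model in order to control for regression to the mean".

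Under Study Parameters, "Additional", the protocol lists seven characteristics: "For confounding and mediating effects, we will collect information on gender, age, marital state, occupational status, duration of illness, medication use and treatment history". It does not commit to adjusting for any of them, and it does not say that they are the only candidates for the rule.

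So the baseline outcome value is settled, and team and centre, the randomisation strata, are levels of the model. Only the additional covariates are left to the rule.

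**The concern.** Allocation is randomised in blocks of 2 and 4 within each team. A significance test of baseline balance is then a poor guide to what belongs in the model. A strongly prognostic variable can be imbalanced enough to matter without reaching significance, and a perfectly balanced one still reduces residual variance. The rule drops both.

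The second condition, correlation with the results, can be checked only once outcome data exist. The primary model is therefore settled after the outcomes are in, and the reported standard error takes no account of the selection step. With no thresholds and no closed list, the text does not determine a single model. At stake are the reproducibility of the primary estimate and some precision.

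**Working it through.** **Reproducing the plan's own figure.** The Sample size section says "the study is powered at 80% to detect an effect size of" d = .5 at two-sided .05 with 63 per arm. n per arm = 2(1.96 + 0.8416)² / 0.5² = 62.8, so 63. Power at 63 is 0.801. The figure is reproduced.

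**How often chance imbalance arises.** With seven independent candidates, the probability that at least one differs at screening level a is 1 − (1 − a)^7: 30% at a = .05, 52% at .10 and 79% at .20. The protocol does not say which level applies. These figures cover the first condition only. The rule also requires correlation with the results, so a covariate enters less often, as shown below.

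**Simulation inputs.**

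- From the protocol: N = 133, 1:1 allocation, two-sided .05, and within-person correlation 0.6, used as the baseline-to-follow-up correlation.
- Assumed: the number and strength of prognostic covariates, screening levels of .05 and .20, a .05 test for correlation with the outcome, a true difference of 0.4 SD, and 15 candidates in one setting.
- Model: single-level ANCOVA with the baseline outcome always included. Team and centre clustering was not modelled.
- Runs in the strong settings: 20,000 null and 6,000 alternative per setting.

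**Type I error under the rule (nominal 0.05), strong settings.**

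| Candidates / prognostic / coefficient | Screen .05 | Screen .20 | Fixed in advance |
|---|---|---|---|
| 7 / 1 / 0.3 | 0.048 | 0.043 | 0.050 |
| 7 / 2 / 0.4 | 0.036 | 0.025 | 0.050–0.052 |
| 7 / 3 / 0.3 | 0.039 | 0.030 | 0.050–0.051 |
| 15 / 4 / 0.3 | 0.034 | 0.021 | 0.047–0.050 |

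The Monte Carlo standard error is √(0.05 × 0.95 / 20,000) = 0.0015. The mildest entry (0.0475 unrounded) is therefore about 1.6 standard errors below nominal, and the others are clearly below it.

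The direction has a simple cause. The rule corrects the estimate in samples with large imbalance but keeps the wider standard error elsewhere. In the second setting (screen .05) the SD of the estimate across null samples is 0.139 with baseline only, 0.129 under the rule and 0.099 with covariates fixed in advance.

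At least one covariate was selected in 6–21% of runs at the .05 screen and in 24–61% at .20.

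**Power: closed form, then simulation.** With baseline only, the residual variance is 1 − 0.6² = 0.64. Adding k independent covariates with coefficient b (in SD units) leaves v = 0.64 − k·b². The standard error is 2√(v/133), and power is approximately Φ(0.4/SE − 1.96). The correlation given baseline is b/0.8, so b of 0.3 and 0.4 correspond to 0.375 and 0.5. The weak settings are stated as correlations r given baseline, so v = 0.64(1 − k·r²). They were run at a standardised difference of .5, read here on the residual-SD scale: 0.5 × √0.64 = 0.4.

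| Prognostic covariates | v | Closed form, fixed in advance | Simulated, rule (screen .05) | Simulated, fixed in advance | Gain (points) |
|---|---|---|---|---|---|
| none (baseline only) | 0.640 | 0.822 | – | – | – |
| one, r = 0.1 | 0.634 | 0.826 | 0.810 | 0.816 | 0.6 |
| one, r = 0.2 | 0.614 | 0.837 | 0.812 | 0.830 | 1.8 |
| two, r = 0.2 | 0.589 | 0.852 | 0.812 | 0.841 | 2.9 |
| one, b = 0.3 | 0.550 | 0.875 | 0.816 | 0.864 | 4.8 |
| three, b = 0.3 | 0.370 | 0.967 | 0.830 | 0.961 | 13.0 |
| two, b = 0.4 | 0.320 | 0.983 | 0.837 | 0.979 | 14.1 |
| four, b = 0.3 (15 candidates) | 0.280 | 0.992 | 0.834 | 0.988 | 15.5 |

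Closed form and simulation agree to within about 1 point. In the strong settings, baseline-only power in the same runs was 0.81–0.82, so the rule loses nothing against baseline-only adjustment and gains slightly. At a .20 screen, rule power was 0.83–0.89, still about 4 to 11 points below covariates fixed in advance. In the weak settings the rule's type I error was 4.6–4.8%.

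**The case against.** The strongest reply is that the rule does little damage. Three parts of it stand.

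- **Error rate.** A reader might infer that choosing covariates from the data raises the false-positive rate. The calculations show none of that: the rate is nominal or below. Inflation would need discretionary use of the unstated thresholds, and taking the smallest p-value across three screening levels still gave about 5% (4.8–5.3%).
- **Power.** A reader might infer that the trial falls short of its target. Power under the rule stays at 81% or more in the settings examined, against a target of 80%. The loss is only relative to a better analysis that the protocol never promised, and it is small if gender, age, marital state and the like add little once baseline NEL is known.
- **Scope.** The baseline value is already fixed, and team and centre are already in the model.

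A reader might also infer that outcomes are inspected by arm before the model is chosen. The protocol does not say so. Imbalance needs arm labels and baseline data, while correlation with the results can be computed on pooled data. What stands is that the model depends on outcome data, not that outcomes are compared by arm beforehand.

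Finally, patients are randomised after verbal agreement, and written consent and baseline measurement follow (Design and Allocation; Recruitment). Loss between these steps could produce differences that are not chance, so comparing the arms at baseline has some diagnostic use. That does not make it a sound way to select covariates.

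None of this answers the remaining defect: the text permits more than one primary model.

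**Conclusion.** The point holds as a weakness of pre-specification with a moderate cost in precision. The protocol itself states the rule, so this is not a detail merely left to an analysis plan. The additional covariates in the primary and secondary models depend on chance imbalance and on outcome data, thresholds and candidates are open, and balanced prognostic variables are discarded.

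Type I error under mechanical application is about 2 to 5%, not inflated. At a .05 screen, the power forgone relative to covariates fixed in advance is about 1 to 3 points if they are weak (r about 0.1 to 0.2 given baseline NEL) and about 5 to 15 points if they are strong (about 0.3 to 0.5). The size rests on assumed correlations, assumed screening levels and a single-level model in place of the planned four-level one. The dependence of the model on the data rests on none of these.

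**What to change.** Delete the selection sentence. Before outcomes are examined, name a short closed list of prognostic baseline covariates from data already collected, for example duration of illness from the list under "Additional". Enter them regardless of imbalance, together with the baseline outcome value and the team and centre levels already planned.

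Keep baseline comparisons descriptive, or use them as a check on loss between randomisation and baseline measurement; they should not decide the model. Present any imbalance-driven adjustment as a labelled sensitivity analysis.

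The cost is two sentences of text and a few degrees of freedom. No new data are needed.

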### **Economic Evaluation**

The economic analysis is also performed according to the intention-to-treat principle. Both a cost-effectiveness analysis (CEA) (outcome NEL) and a cost-utility analysis (CUA) (effects expressed as QALY's, based on EuroQol utility score) will be done. Primary outcome parameters are the proportion of increased quality of life measures (CEA), and total QALY gained during 18 months (CUA). We will adapt a societal perspective, including the costs of all types of health services and the costs that stem from production losses. The time frame of this study is restricted to 18 months. Therefore, we will not correct for inflation and will not discount costs. All costs are expressed in euros (e) for the reference year 2016.

Robustness and uncertainty around the cost-effectiveness ratio (ICER) are determined by non-parametric bootstrapping. The point estimation of the ICER and the results of the bootstrap analyzes are graphically displayed in a cost-effectiveness plane in order to assess whether the RG appears to be acceptable from a cost-effectiveness perspective. Also, sensitivity analyses will be performed to test the robustness of the results. Some sensitivity analyses are: analyzing only data from study completers (patients who have complete data sets at all three assessments), analyzing costs when the more narrow perspective of direct costs is used (instead of the broader societal perspective), and correcting for baseline costs and utilities. Results are described in accordance with the CHEERS guidelines for economic health evaluations (Husereau et al., 2013).

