### **Design and Allocation**

The study is a multicenter randomized clinical trial (MRCT), including 180 patients of nine Dutch mental health care centers.

An independent statistician of the Trimbos Institute will generate a computerized allocation list, stratified on mental health care centers and teams. That is, for each team of every mental health care center a separate allocation sequence will be generated by means of allocation blocks assuming a maximum of fourteen participants per team. Two sizes of allocation blocks are used (i.e. 2 and 4), yielding three possible cells (i.e.: 2x4 and 2x2; 1x4 and 5x2; 0x4 and 7x2). These cells in turn, are randomized to keep the allocation unpredictable for the different stakeholders (care-givers and researchers). In order to minimize the risk of imbalance between conditions, the ratio of these possibilities will be stratified on resp. 1:2:2. The allocation sequence will be stored with the independent statistician and is concealed from all researchers, caregivers, and participants. Once allocated, condition is passed on to the central researcher and local staff by email so that the local intake procedure can be continued. Further matching between patient and case manager is allowed and performed by the local staff of the FACT-team. At start of the baseline measurement (0 months), written informed consent is obtained. Further assessments take place 9 (T1) and 18 (T2) months after obtaining informed consent.. Local independent research assistants will carry out all assessments. Assessments comprise self-report questionnaires (administered on PC) and interviews, see Table 1 and Table 2. Given the nature of our study, blinding of participants and treating clinicians is not possible. The local research assistants however are blinded. To optimize similarity in assessments, research assistants use an extensive standardized study protocol and discuss process in regular telephonic and face-to-face meetings with the central researcher.

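### Baseline utility and costs are corrected for only in a sensitivity analysis, so the main cost-utility result is, by implication, less precise than the collected data allow

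*Protocol*

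**What the plan says.** Under Statistical analyses, Economic Evaluation, the protocol plans a cost-effectiveness and a cost-utility analysis by intention to treat, from a societal perspective, with a bootstrapped ICER. The cost-utility outcome has its "effects expressed as QALY's, based on EuroQol utility score" and is described as "total QALY gained during 18 months (CUA".

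The section then announces robustness checks: "Also, sensitivity analyses will be performed to test the robustness of the results". The examples are a completers-only analysis, a direct-cost perspective, and "correcting for baseline costs and utilities". Baseline utility and baseline costs appear nowhere else in the planned economic analysis.

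The neighbouring section, Effectiveness RG, treats baseline differently: "Baseline values of the parameters will be included in the model in order to control for regression to the mean". It also has a covariate rule: "Variables that show different distributions in the conditions, and are correlated with the results, are included in the analysis as a covariate". Both statements concern the effectiveness outcomes. The economic section carries over only the intention-to-treat principle.

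The baseline data exist. Table 2 schedules EQ-5D-5L and TIC-P at 0, 9 and 18 months, and Design and Allocation confirms the timing: "Further assessments take place 9 (T1) and 18 (T2) months after obtaining informed consent".

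**The concern.** A correction listed as a departure from the main analysis is, by implication, not part of it. For QALYs this matters more than for most outcomes. Under the usual area calculation the baseline utility is itself part of the total, and it also predicts both follow-up utilities. Leaving it out of the main model leaves explainable variation in the QALY difference.

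Cost-effectiveness is the trial's secondary objective, and the protocol intends to judge acceptability from the ICER and its bootstrap scatter. If the adjusted and unadjusted results differ, the plan as written makes the less precise one the headline. The protocol gives no reason for treating the economic outcomes differently from the effectiveness outcomes.

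**Working it through.** The economic section states no figure to reproduce. The trial's one closed-form figure, 63 per condition in Sample size, does reproduce (2 × (1.96 + 0.84)² / 0.5² = 62.7, rounded up), but nothing here depends on it.

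**Inputs**
- Visits at 0, 0.75 and 1.5 years (Design and Allocation; Table 2).
- Final sample 158 (Small changes made to the original protocol), taken here as two equal arms with complete utilities.
- Correlation between visits ρ = 0.6 (Sample size). There it is a planning assumption for the primary outcome; using it for utility is an assumption of this check, so 0.4 to 0.8 is shown.
- Utility SD, equal at all visits. It is not in the document; 0.25 is assumed, range 0.20 to 0.30. The percentage cuts below do not depend on it.
- QALY formula. The protocol gives none, so two readings are checked.

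**Reading A: trapezium area.** QALY = 0.375·u0 + 0.75·u9 + 0.375·u18. In units of SD²:
- Variance = 0.84375 + 1.40625ρ
- Slope on baseline utility = 0.375 + 1.125ρ
- Residual variance = variance − slope²
- Adjusted SE / unadjusted SE = √(residual / variance)

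**Reading B: gain over the patient's own baseline.** Subtracting 1.5·u0 gives weights −1.125, 0.75 and 0.375. The slope becomes −1.125 + 1.125ρ and the variance 1.96875 − 1.96875ρ.

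| Reading | Correlation | Variance | Slope | Residual | SE ratio | Cut in SE |
|---|---|---|---|---|---|---|
| A | 0.4 | 1.40625 | 0.825 | 0.7256 | 0.718 | 28% |
| A | 0.6 | 1.6875 | 1.05 | 0.585 | 0.589 | 41% |
| A | 0.8 | 1.96875 | 1.275 | 0.3431 | 0.417 | 58% |
| A | 0.6 between adjacent visits, 0.36 from 0 to 18 months | 1.62 | 0.96 | 0.6984 | 0.657 | 34% |
| B | 0.4 | 1.18125 | −0.675 | 0.7256 | 0.784 | 22% |
| B | 0.6 | 0.7875 | −0.45 | 0.585 | 0.862 | 14% |
| B | 0.8 | 0.39375 | −0.225 | 0.3431 | 0.934 | 7% |

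The residual variance at a given correlation is the same under A and B. The two totals differ only by 1.5·u0, so once u0 is in the model the arm effect is identical. Adjustment therefore also removes the ambiguity about what is meant by QALYs gained.

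**Exposure to chance imbalance.** The SE of the baseline utility difference is 0.25 × √(4/158) = 0.040. Under A at ρ = 0.6, an imbalance of one SE is expected to move the QALY difference by 1.05 × 0.040 = 0.042 (0.033 to 0.050 for SD 0.20 to 0.30). Of this, 0.375 × 0.040 = 0.015 is mechanical and the rest comes through correlation. Under B the shift is −0.45 × 0.040 = −0.018, with the opposite sign. The SE of the QALY difference under A is √1.6875 × 0.040 = 0.052 unadjusted and √0.585 × 0.040 = 0.030 adjusted.

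**Costs.** Baseline costs precede the 18-month window and act only through their correlation with later costs. The document gives no such correlation, so no figure is offered for costs or for the ICER.

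**The case against.** The strongest reply is that nothing is omitted or biased. The adjusted analysis is already planned, so readers will see both results. Allocation is randomised within centres and teams, so the unadjusted difference is unbiased over repetitions, and a bootstrap of it already reflects chance baseline variation. This stands. A reader might infer that the plan ignores baseline, or that the headline ICER is biased. The protocol supports neither: it foresees the correction, and it reports no baseline imbalance. What remains is efficiency, and error conditional on the imbalance that this trial happened to have. An unadjusted bootstrap removes neither.

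A reader might also infer that a baseline difference passes in full into the QALY difference and the ICER. That goes too far. Only the 0.375 weight is mechanical, and it belongs to the trapezium reading. The rest depends on an assumed correlation, and baseline costs have no mechanical route at all. The cost-effectiveness analysis on the empowerment scale does not use utilities.

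Finally, the main analysis is unadjusted by implication rather than by statement, and model detail may sit in a statistical analysis plan that is not shown. That is fair for the QALY formula and the regression form. It is weaker for the choice of which analysis leads, because the protocol itself puts baseline correction in the sensitivity list.

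**Conclusion.** The point holds as one of precision and of which analysis leads, not of bias. By implication the main cost-utility analysis and its ICER are unadjusted for baseline values that the trial collects and that its effectiveness models use. At a correlation of 0.6, adjustment would cut the SE of the QALY difference by about 41% under the trapezium area (28% to 58% for correlations of 0.4 to 0.8; about 34% if the correlation decays to 0.36 at 18 months). If QALYs gained means gain over own baseline, the cut is only about 14%. These figures rest on a correlation borrowed from the primary outcome, equal utility variances across visits and complete data. The gain for costs and the ICER is unquantified. The primary effectiveness result is not affected.

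**What to change.** Make the baseline-adjusted analysis the main economic analysis: regress QALYs on arm plus baseline utility, and costs on arm plus baseline costs, and refit both in each bootstrap draw so that the ICER and its scatter come from the adjusted differences. State the QALY formula. Keep the unadjusted comparison as a sensitivity analysis.

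No new data are needed, but the change is not free. The protocol's note of changes, dated June 2021, already reports the final sample and the mode of the last 18-month assessments. A swap made after data collection alters the headline analysis, so it must be declared as a change to the plan with its reason, and both results reported. Beyond that declaration the cost is a little more analysis work.
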